### Biobank

Blood, tissue, and fecal swab samples collected during the trial will be stored in the Bio- and Genome Bank, Denmark. Residual blood and tissue biopsies as well as clinical and sequencing data will be transferred to the Renal Cancer Research Biobank at Aarhus University Hospital for future research, where it will be saved and stored in a pseudonymized form.

### Dissemination

Any protocol modifications will be reported timely to the relevant authorities, investigators/centers, and if necessary, patients. No protocol modification is effected before the necessary approval have been given. Results from the NORDIC-SUN trial will be published in peer-reviewed scientific journals.

## Discussion

For synchronous mRCC, the question whether the primary tumor responds just as well as the remaining systemic disease to combinational IO-IO or TKI-IO treatment remains. Moreover, the timing of surgery versus systemic treatment is still debated. The impact of debulking the primary tumor in patients with synchronous mRCC has been evaluated in two prospective randomized studies in the TKI era. The SURTIME trial questioned the timing of CN, upfront or deferred, and reported that unnecessary surgery could be avoided through pre-treatment with sunitinib to identify patients inherently resistant to systemic targeted therapy [13]. The CARMENA trial tested the benefit of initial nephrectomy and showed no benefit of upfront nephrectomy over sunitinib alone [12]. As 20% of the patients in the sunitinib alone arm in CARMENA had a deferred CN, both SURTIME and CARMENA can be regarded as proof-of-concept trials demonstrating that patients who require systemic therapy should receive drug therapy first with the option to be offered deferred CN after disease consolidation. Now that the preferred treatment for mRCC has changed to favoring doublet IO or TKI-IO, the role of deferred CN in this setting is yet to be determined.

In the presented randomized clinical trial, the NORDIC-SUN trial, the role of surgery will be determined in both poor and intermediate risk patients. It is expected that the initial first-line of IO-IO or TKI-IO treatment will reduce the IMDC risk score for some patients, thereby making more patients eligible for surgery. Similarly to the NORDIC-SUN trial, the Prospective Randomized Open Blinded Endpoint (PROBE) trial (NCT04510597) has been initiated to evaluate if CN provides an overall survival benefit in patients responding to first-line systemic therapy (objective response or stable disease) [22]. The PROBE trial tests CN and systemic therapy (IO-IO or TKI-IO) against systemic therapy alone. Enrollment started in 2021 and the study is expected to be completed in 2033. Comparison of the results from these two trials would be warranted.

We hypothesize that deferred CN after initial immunotherapy-based first-line treatment will improve OS in patients with synchronous metastatic RCC and ≤ 3 IMDC risk features. Furthermore, this study will identify potential predictive and prognostic biomarkers based on immune subsets in blood and tumor, gene expression, tumor mutational burden, overall genetic alterations, ctDNA, and gut microbiome. Our findings aim at helping clinicians to stratify patients more accurately for surgery and/or immunotherapy-based combinational treatment.

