## Background

### Cytoreductive nephrectomy in synchronous metastatic renal cell carcinoma patients

Around 20% of patients with Renal Cell Carcinoma (RCC) have synchronous metastatic disease at diagnosis, i.e. are diagnosed with a primary kidney tumor and metastases simultaneously. Patients presenting with metastatic disease at primary diagnosis have the worst prognosis due to underlying aggressive tumor biology and are often clinically challenging due to symptoms from either the primary tumor or the metastases [1, 2]. The critical question is whether the primary kidney tumor should be removed in patients with de novo, synchronous, mRCC.

In the clinic, mRCC patients are stratified into ‘favorable’, ‘intermediate’, and ‘poor’ prognostic risk groups according to 0, 1–2, or 3–6 international metastatic renal cell carcinoma database consortium (IMDC) risk factors, respectively, with the majority (95%) of de novo synchronous mRCC patients belonging to the intermediate or poor risk group [2, 3].

Despite the improvements that targeted treatment and checkpoint immunotherapies have brought to mRCC, response rates are still overall poor across patients (reviewed in [4]). Surgical resection of the primary tumor (cytoreductive nephrectomy, CN) upon metastatic spread at diagnosis is currently recommended following systemic therapy for patients with a good general health condition, few IMDC risk factors (maximum of three), and a response to systemic therapy [5, 6]. The concept is that CN combined with systemic therapy may result in no evidence of disease and eliminate a potential source of immunosuppressive or tumor-promoting growth factors [7–9]. On the other hand, if performed initially, there is a risk for operated patients never to receive or benefit from systemic therapy due to complications following CN or rapid tumor progression, due to having their commencement of systemic treatment delayed because of surgery complications, or due to hampering of the immune response following antibiotic treatment after surgery [10]. Recently, a post hoc analysis from the JAVALIN renal 101 phase 3 trial indicated that CN may improve OS in synchronous metastatic patients receiving tyrosine kinase inhibitor and immunotherapy (TKI-IO) treatment [11].

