### Randomization and masking

Patients are randomized 1:1 into the two treatment arms:ARM A: 3 months of IO-IO or TKI-IO followed by deferred CN, followed by maintenance nivolumab or a TKI-IO-combination.ARM B: No surgery, 3 months of IO-IO or TKI-IO followed by maintenance nivolumab or a TKI-IO-combination.

Patient eligible for surgery is randomized by a local project nurse using a computer-generated allocation sequence and is not blinded due to the circumstances; surgery versus no surgery. In Arm A patients are treated according to standard protocol with first-line IO-IO or TKI-IO combination treatment followed by a CN. In Arm B patients are receiving standard IO-IO or a TKI-IO combination first-line treatment (Fig. 1). Patients will be stratified by treatment choice (IO-IO vs TKI-IO).

The remaining patients, referred to as Arm C, not eligible for randomization due to > 3 IMDC risk factors, progressive disease at metastatic sites, poor performance or a non resectable tumor will undergo three months of nivolumab or a TKI-IO combination and then be evaluated again after another 3 months. If still not eligible for randomization, the patients will continue nivolumab maintenance and TKI-IO combination and be followed on survival.

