### Statistical analyses

#### Sample size determination

Sample size calculations are based on simulated survival data and cox regression. With the assumption that 60% of patients meet the randomization criteria, and to demonstrate a 50% improvement in OS, with a 3-year follow-up, a sample size of 400 patients is needed to achieve 80% power at a 5% significance level. Hence, 400 patients will be included in NORDIC-SUN with the estimation of 240 patients (60%) being randomized (120 in each arm) and 168 occurred deaths upon reach of appropriate power.

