#### Data analysis

Difference in primary and secondary endpoints between the two treatment arms will be tested with a two-sided log rank test at the 5% alpha level. Statistical methods including Kaplan–Meier and cox proportional hazard regression will be performed adjusted and unadjusted for the stratification factor. Furthermore, linear regression, logistic regression, and machine learning approaches (e.g. Random Forest, Neural Networks, and Gradient Boost models) will be applied in an exploratory manner to identify any correlation between molecular measures and clinical outcome parameters.

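### The 80% power is stated with no allowance for nephrectomy in the no-surgery arm, and at a hazard ratio of 0.667 the 168 deaths give about 75% even without any

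*Protocol article*

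**What the plan says.** All references are to the protocol article.

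- **Sample size determination.** The inputs listed are the randomised share ("With the assumption that 60% of patients meet the randomization criteria") and the effect and follow-up ("to demonstrate a 50% improvement in OS, with a 3-year follow-up"). The result is that "a sample size of 400 patients is needed to achieve 80% power at a 5% significance level", expected to yield "240 patients (60%) being randomized (120 in each arm) and 168 occurred deaths". The method is simulation with Cox regression. No rate is given for surgery in Arm B or for omitted surgery in Arm A, and 240 is exactly 60% of 400.
- **Data analysis.** The arms are compared with a "two-sided log rank test at the 5% alpha level".
- **Randomization and masking.** The control arm is "ARM B: No surgery, 3 months of IO-IO or TKI-IO followed by maintenance nivolumab or a TKI-IO-combination". Allocation is not blinded.
- **Study procedure.** Patients are randomised only if judged suitable for surgery, with at most three IMDC factors and no progression at metastatic sites.
- **Background, first subsection.** Removal of the primary tumour "is currently recommended following systemic therapy for patients with a good general health condition, few IMDC risk factors (maximum of three), and a response"; the response meant is that to the drug treatment already given.
- **Discussion.** On the earlier randomised trial of initial nephrectomy: "As 20% of the patients in the sunitinib alone arm in CARMENA had a deferred CN".

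**The concern.** Every Arm B patient has been judged operable at a multidisciplinary meeting, and patient and surgeon both know the allocation. Those who respond to systemic therapy meet the conditions under which the article itself says deferred nephrectomy is currently recommended. Some nephrectomies in Arm B are therefore foreseeable, and the article reports a precedent rate from a drug-only arm. The power statement mentions neither.

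Analysis by randomised arm stays valid under crossover, but the difference between arms shrinks towards none and power falls. The trial would then be more likely to miss a real benefit than the stated 80% suggests. Omitted surgery in Arm A acts in the same direction.

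Crossover also affects which comparison is meant. The Primary endpoint section describes the groups by whether surgery was received, while Data analysis compares the treatment arms. The two coincide only when everyone follows the allocation.

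**Working it through.** **Inputs.** From the article: two-sided alpha 0.05, 1:1 allocation, 240 randomised, 168 deaths, 80% power, 50% improvement. Assumptions: proportional hazards, with the 50% improvement read as HR = 1/1.5 = 0.667 (|ln HR| = 0.4055); Arm B crossover rate c of 10%, 20% or 30%, of which only 20% has a source in the article.

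**Step 1: reproduce the stated figure, no crossover.**

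Deaths for 80% power (Schoenfeld): D = 4 × (1.960 + 0.842)² / (ln HR)² = 4 × 7.849 / 0.1644 = 191. Freedman's formula gives 197.

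Power at 168 deaths: Φ(|ln HR| × √168 / 2 − 1.960) = Φ(0.4055 × 6.481 − 1.960) = Φ(0.668) = 74.8%. Freedman gives 73.6%. A log-rank simulation gives 74–75% (120 per arm, exponential survival, 4,000 runs; assumed 3-year accrual and 3-year follow-up, control median of about 24.7 months chosen to give 168 deaths).

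The stated 80% is not reproduced. Other readings do not settle it:

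- A one-sided 5% test gives 83.7% at 168 deaths and conflicts with Data analysis.
- HR 0.50 needs only 66 deaths.
- HR 0.649 gives exactly 80% at 168 deaths, but that is a 54% improvement (1/0.649 = 1.54).

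**Step 2: add crossover in Arm B, taking 0.667 as the full-adherence effect.** Two simple models, both with full benefit from randomisation:

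- hazard mixing: HR* = 0.667 / [(1 − c) + 0.667c]
- log-HR dilution: HR* = 0.667^(1 − c)

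For c = 0.20, mixing gives 0.667 / 0.933 = 0.714 and dilution gives exp(−0.8 × 0.4055) = 0.723. Power is Φ(0.3365 × 6.481 − 1.960) = Φ(0.221) = 58.7% and Φ(0.3244 × 6.481 − 1.960) = Φ(0.142) = 55.7% respectively.

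| Arm B crossover | HR* (mixing / dilution) | Power at 168 deaths | Deaths for 80% |
|---|---|---|---|
| 0% | 0.667 | 75% | 191 |
| 10% | 0.690 / 0.694 | 67% / 66% | 228 / 236 |
| 20% | 0.714 / 0.723 | 59% / 56% | 278 / 299 |
| 30% | 0.741 / 0.753 | 49% / 45% | 349 / 390 |

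At 20% and above, the deaths needed exceed the 240 patients randomised, so longer follow-up alone could not restore 80%.

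**Step 3: timing.** The same simulation, stopped at 168 deaths with 20% crossover, gives 55% if surgery falls at randomisation, about 60% if 6 months later and about 62% if 12 months later.

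**Step 4: sensitivity to the design effect.** Starting from HR 0.649, which gives 80% at 168 deaths, 20% crossover gives 0.649^0.8 = 0.708 and 61% power.

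**The case against.** The strongest objection is that the article is silent, and silence is not an assumption. It condenses a full protocol, its simulation settings are not shown, and the 50% improvement could already be the difference expected between the arms as randomised. If so, diluting it again counts crossover twice. This stands. A reader might infer that the calculation assumes full adherence, but the article does not say so. What can be said is that no allowance is stated, and that if 0.667 is the full-adherence effect none can be hidden in the figures, because 168 deaths is already below the 191 needed with no crossover.

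The 20% does not transfer directly either. It comes from a TKI-era trial of initial nephrectomy, and the article does not say why those patients were operated on. The rate here could be lower or higher. The recommendation in the Background also requires a response, whereas randomisation requires only absence of metastatic progression, so it covers part of Arm B and not all of it.

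Two further inferences fail. One is that crossover explains the whole fall from 80% to below 60%. About 5 points (80% to 75%) come from the death count before any crossover; at 20% the crossover itself costs about 16 to 19 points from that baseline. The other is that the article regards the earlier trial as contaminated. The Discussion uses the 20% to support giving drug therapy first with optional deferred surgery, and the weaknesses the Background names are low power and an earlier treatment era.

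Finally, crossover-adjusted estimators, data-collection items for off-arm surgery, central review of its rate and the handling of time to subsequent therapy are commonly left to the full protocol or analysis plan. Their absence here is no finding.

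**Conclusion.** The point holds in a limited form. The stated 80% does not follow from the stated 168 deaths when a 50% improvement is read as HR 0.667: power is about 75% with no crossover. It therefore has no margin for nephrectomy in Arm B, which the article's own Background and Discussion make foreseeable. If 0.667 is the full-adherence effect, power at 168 deaths is about 66–67% at 10% crossover, 56–59% at 20% (up to about 62% with surgery 6 to 12 months after randomisation) and 45–49% at 30%.

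These figures rest on proportional hazards, full benefit of surgery in patients who cross over, and assumed crossover rates. If the sponsor meant the 50% as the as-randomised effect, the losses from crossover do not apply, but the shortfall to about 75% remains. The documents do not support saying that 20% crossover will occur, or that the trial was planned on perfect adherence.

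**What to change.** No additional enrolment is needed.

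1. State whether the 50% improvement is the effect under full adherence or the as-randomised effect net of crossover, and give it as a hazard ratio.
2. Restate the power at 168 deaths with no crossover, and over Arm B crossover of 10% to 30%, identifying the source of the 20% and its limits.
3. Keep the comparison by randomised arm as the primary survival test, and word the Primary endpoint section to match.

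The cost is a less favourable stated power. The calculation itself is short, and nothing in treatment or recruitment changes.

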## Conclusion

Patients with de novo, synchronous metastatic disease are clinically challenging. The NORDIC-SUN trial is a randomized clinical trial evaluating the effect of deferred CN during first-line immunotherapy doublet or TKI-IO treatment only in synchronous metastatic RCC patients. The trial will identify potential predictive and prognostic biomarkers, thereby seeking to personalize the treatment for each patient.

## Data Availability

Future data from the trial will be available after publication of trial results from the corresponding author on reasonable request.

## Abbreviations

CN: Cytoreductive nephrectomy
ctDNA: Circulating tumor DNA
DCR: Disease control rate
IMDC: International metastatic renal cell carcinoma database consortium
IO: Immunotherapy
PFS: Progression free survival
RCC: Renal cell carcinoma
mRCC: Metastatic renal cell carcinoma
Nivo: Nivolumab
ORR: Objective response rate
OS: Overall survival
TKI: Tyrosine kinase inhibitor
TST: Time to subsequent systemic therapy
